### Survey data

Pre- and post-intervention surveys on food insecurity, diet quality, depression, as well as self-efficacy for healthy eating, healthy weight, and chronic disease management will be administered at baseline and at the 16-week follow-up visit. Surveys were compiled from the below validated instruments:The Hunger Vital Sign: assesses household food insecurity (*Hager et al.*, 2010).Eating at Americas Table Survey: assesses diet quality (*Borgonovi et al.*, 2022).Patient Health Survey Depression Scale: valid diagnostic and severity measure for depressive disorders (Kroenke *et al.*, 2009).Healthy Eating and Weight Self-Efficacy Scale: assesses individuals’ ability to maintain a healthy weight and eating pattern (Wilson-Barlow *et al.*, 2014).Self-Efficacy for Managing Chronic Diseases Scale: a six-item questionnaire that determines self-efficacy as one takes an approach to improve health behaviors to managing varying chronic diseases (Ritter and Lorig, 2014).

In addition, the post-intervention survey contains 11 non-validated items assessing adequacy, practicality, and satisfaction with healthy meals or produce box received by participants. These additional non-validated items were developed by the first author.

### Data analysis

The independent variables in this study are study arm (healthy meals, produce box, and matched controls [standard of care]), nutrition counseling and education, and time (pre-intervention, 16 weeks, six months and 12 months). The primary dependent variable (outcome) is absolute weight change at 16 weeks between groups. The secondary dependent variables (outcomes) are as follows: i) absolute weight change at six months and 12 months from baseline; ii) change in hbA1c, dosage, and number of diabetes medications; iii) change in dosage and number of blood pressure medications, and; iv) change in numeric rating from baseline to 16 weeks for food insecurity, diet quality, depression as well as self-efficacy for health eating, healthy weight, and chronic disease management. A final outcome of interest is satisfaction rating for the interventions provided in the study, measured using a non-validated questionnaire developed for this study.

Descriptive statistics will be calculated for demographic data and for each dependent variable by group, nutrition counseling and education, and time. Separate repeated-measures ANOVAs will be conducted for each dependent variable with the between subjects factor group (healthy meals, produce box, and matched controls) and the within subjects factor time (pre-intervention and 16 weeks). *Post hoc* testing will be conducted as appropriate. Effect sizes will be calculated between pre-intervention and 16 weeks to capture the changes from pre- to post-intervention. Missing data will be analyzed using an intention-to-treat strategy. Statistical analysis will be performed by a biostatistician using SAS statistical software. The biostatistician will be blinded to the intervention for each group to eliminate potential bias during data analysis.

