## Methodology

### Study aims

The primary aim of this study is to compare absolute weight change among participants receiving daily healthy meals or produce box versus matched controls (standard of care) at 16 weeks from baseline:This aim tests the hypothesis that receiving daily healthy meals will result in greater absolute weight loss compared to receiving a produce box or standard of care at 16 weeks from baseline.This aim tests the hypothesis that receiving either daily healthy meals or a produce box will result in greater absolute weight loss compared to standard of care at 16 weeks from baseline.
The secondary aim of this study is exploratory and will compare daily healthy meals or produce box versus matched controls in improving chronic disease markers:This aim tests the hypothesis that receiving daily healthy meals will result in greater improvement in hbA1c and blood pressure compared to receiving a produce box or standard of care box at 16 weeks, six months, and 12 months from baseline.This aim tests the hypothesis that receiving either daily healthy meals or a produce box will result in greater improvement in weight, hbA1c and blood pressure compared to standard of care at 16 weeks, six months, and 12 months from baseline.
To assess whether receiving daily healthy meals or a produce box in conjunction with nutrition counseling and education results in improvement in food insecurity, diet quality, depression, self-efficacy for healthy eating and healthy weight, and self-efficacy for chronic disease management from baseline to 16 weeks.

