### Study design

This study is a parallel-arm quasi-randomized control trial with nonequivalent matched controls, which will be conducted between January 2022 and December 2023. Seventy adult patients recruited from our ambulatory practice will be randomly assigned to receive either: i) daily healthy frozen meals or ii) a weekly produce box and recipes for 15 weeks. Each study arm will comprise 35 patients with a documented diagnosis of obesity (body mass index [BMI] equal to or greater than 30kg/m^2^) and one or more of the following conditions: pre-type 2 diabetes/type 2 diabetes or hypertension. Participants will complete an in-person baseline visit and a follow-up visit at 16 weeks from baseline, and their medical charts will be reviewed for trends in these biomarkers at six months and 12 months from baseline. Healthy meals or a produce box will be shipped to the home address of participants once a week. Healthy meals provided in the study are low-sodium and diabetic-friendly ready-to-heat and serve breakfast, lunch, and dinner items. The produce box provided in the study will comprise fresh vegetables and fruits. For participants receiving a produce box, recipes utilizing items contained in the box will be available at the vendor’s website.

All participants will complete one individual medical nutrition therapy session via phone with a dietitian. The individual medical nutrition therapy appointment will occur within two weeks of enrollment in the study. A total of four nutrition and health videos, each under 10 minutes in length, will be available for participants to view between weeks 3 and 15 of the study. The complete study procedures are outlined in Table 1. Participants will be required to view the videos on healthy eating and weight loss and, as applicable to their health status, videos on type 2 diabetes and hypertension (see Table 2). The Healthie application (https://www.gethealthie.com/?afmc=a46i) will be utilized for nutrition education programming. Through the Healthie application, participants will receive automated text and/or email reminders to view educational videos. This feature is designed to drive compliance and completion of the nutrition education component. A report will be generated to provide completion percentage and other details based on participant engagement. The Healthie application is compliant with the US Health Insurance Portability and Accountability Act.

**Table 1. tbl1:** Schedule of study activities

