### Study population

Current patients at our ambulatory practice who are 18 years and older, and are of any gender and race, are eligible for enrollment in the study. Patients who have food allergies, are pregnant or planning to become pregnant, have no access to internet, or require English language interpretation will be excluded from participation. Additional exclusion criteria are participation in nutrition counseling with our partnering organization within the past six months, current participation in a structured weight loss program, or current use of weight loss medications. Medications prescribed for other conditions but that may have a weight loss effect, for example, metformin or GLP-1 agonists prescribed for diabetes treatment or topiramate prescribed for migraine headaches, will not result in the exclusion of potential participants.

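### The comparison of food insecurity and depression between the randomised arms uses unadjusted all-participant change, so participants already at the floor dilute it by an unknown amount

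*Protocol article*

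**What the plan says.** The third aim (Study aims) asks whether meals or a produce box, together with counseling and education, "results in improvement in food insecurity, diet quality, depression" and the self-efficacy ratings between baseline and 16 weeks.

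Entry is set by other conditions. Under Study design, "Each study arm will comprise 35 patients with a documented diagnosis of obesity" and "one or more of the following conditions: pre-type 2 diabetes/type 2 diabetes or hypertension". Study population adds that "Current patients at our ambulatory practice who are 18 years and older, and are of any gender and race, are eligible for enrollment", followed by exclusions that mention neither food insecurity nor depression.

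Under Survey data, "The Hunger Vital Sign: assesses household food insecurity", and a depression scale described as a severity measure is also used. Data analysis defines the outcome as "change in numeric rating from baseline to 16 weeks for food insecurity, diet quality, depression as well as self-efficacy" and states that "Separate repeated-measures ANOVAs will be conducted for each dependent variable with the between subjects factor group" and a within-subjects factor for time (pre-intervention and 16 weeks). It names no baseline covariate and no analysis of participants affected at baseline. Strengths and limitations says that the study population faces food insecurity, but gives no percentage. Nothing is said about how common depression is.

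**The concern.** Someone who is food secure at baseline, or who has the lowest depression score, can only stay the same or get worse. If a share p of participants is affected and improves by d on average, and the rest do not change, the mean change over everyone is p × d. The same mean can come from a strong effect in a few people or a weak effect in many.

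With two arms and two time points, the group-by-time test is a comparison of mean change. A true difference d between the arms among affected participants therefore also appears as p × d, with the unaffected adding variability but no signal. A flat comparison between meals and produce could be read as no difference in relieving food insecurity or low mood when affected participants did differ. The article fixes both the outcome form and the test, so this concerns a stated choice rather than an omitted detail.

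**Working it through.** **The plan's own figures.** None is given for these outcomes. The sample size concerns weight only. A one-way ANOVA with means 92, 78.4 and 85.2 kg, SD 16 and alpha 0.05 gives power 0.789 at 27 per group and 0.805 at 28, so the stated 28 reproduces. It says nothing about the survey outcomes.

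**Inputs.** From the article: 35 per arm, two randomised arms, all-participant change. The controls come from chart review and no survey of them is described, so the comparison that can be made is between the two randomised arms. Assumed, because the article has no values: a yes/no food-insecurity result; 80% of affected participants resolved in one arm and 40% in the other; 5% new onset among the unaffected in both; baseline prevalence p.

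**Mean change.** For resolution r, the mean is −p·r + 0.05(1 − p) and the variance is p·r + 0.05(1 − p) − mean². At p = 0.4:
- Arm with 80% resolved: mean −0.32 + 0.03 = −0.29; variance 0.35 − 0.0841 = 0.2659.
- Arm with 40% resolved: mean −0.16 + 0.03 = −0.13; variance 0.19 − 0.0169 = 0.1731.
- Difference 0.16; standard error √((0.2659 + 0.1731)/35) = 0.112; ratio 1.43. Approximate power is Φ(1.43 − 1.96) = Φ(−0.53), about 30%.

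The difference among affected participants is 0.40, so 0.16 is p × 0.40.

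**Simulated power for the arm comparison** (figures move by a point or two between runs):

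| Baseline prevalence | All-participant change, as planned | Affected at baseline, Fisher exact | All participants, baseline-adjusted |
|---|---|---|---|
| 20% | 13% | 21% | 20% |
| 30% | 21% | 37% | 34% |
| 40% | 29% | 50% | 48% |
| 50% | 39% | 61% | 61% |
| 80% | 73% | 84% | not needed here |

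**Pooled pre-post change in all 70, same assumptions.** At p = 0.4 the mean is −(0.29 + 0.13)/2 = −0.21 and the variance (0.35 + 0.19)/2 − 0.0441 = 0.2259. The standard error is √(0.2259/70) = 0.0568 and the ratio 3.70, so power is about 96%. By simulation, power is about 37% at 20% prevalence, 79% at 30%, 96% at 40% and above 99% at 50%.

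**A smaller effect on a continuous scale.** Let affected participants differ by d = 0.5 SD, with the SD of change 1 among them and s0 = 0.3 to 1.0 among the rest. The mean is p·d and the variance p + (1 − p)s0² + p(1 − p)d². At p = 0.5 and s0 = 1 this is 0.25/√1.0625 = 0.243 SD, and 35 per arm gives 17% power.

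| p | Arm comparison, everyone | Arm comparison, affected only |
|---|---|---|
| 0.2 | 7–11% | 14% |
| 0.5 | 17–26% | 31% |
| 0.8 | 37–43% | 45% |

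Here the pooled pre-post test in all 70 has 36–63% power at p = 0.4 and 90–95% at p = 0.8. Its robustness from 40% upward therefore also rests on the large effect assumed earlier.

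**Depression.** With equal variances at both visits and correlation ρ, the variance of unadjusted change is 2σ²(1 − ρ), and that of the baseline-adjusted score is σ²(1 − ρ²). The ratio of adjusted to unadjusted is (1 + ρ)/2: 0.75 at an assumed ρ of 0.5, and never above 1. Restricting to those above a screening threshold instead discards participants with milder symptoms who can still improve. Simulation under one assumed score model pointed the same way (power 20–91% for the above-threshold subset, 59–95% for the adjusted analysis of everyone). Only the direction should be relied on.

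**The case against.** The third aim is worded as improvement from baseline to 16 weeks and, unlike the first two aims, names no comparator. Read as pooled pre-post change, the planned analysis is already strong at moderate prevalence if the effect is large. This stands, and it limits the point to the comparison between arms. That comparison is part of the stated ANOVA and is the only one protected by randomisation.

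The average effect over everyone enrolled is a legitimate target, and these are secondary outcomes in a weight trial. Both statements are true. They argue for keeping the all-participant result, not for leaving it as the only one. The subset would hold about 7 to 18 people per arm at 20% to 50% prevalence, and baseline adjustment in everyone gives nearly the same gain at 5% onset. So the subset's advantage over adjustment is its direct reading, not its power.

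A reader might infer that unaffected participants swamp the result, or that the mean change reflects mainly who enrolled. The documents do not support this. No prevalence is given, the article suggests that food insecurity is not rare in this population, and in p × d both factors count equally. A reader might also extend the subset remedy to depression. That is not supported, because only the lowest score is a floor on a severity scale.

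The yes/no result is an assumption. The article speaks of a numeric rating, which may allow partial improvement.

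**Conclusion.** The point holds for the comparison between meals and produce. Unadjusted all-participant change dilutes any difference among affected participants in proportion to baseline prevalence, which the article neither controls nor states. Under the assumed 80% versus 40% resolution, 5% onset and 35 per arm, power is about 13–39% as planned against 21–61% among those food insecure at baseline, for prevalence of 20–50%. At 80% prevalence the gap narrows to 73% against 84%. With a smaller effect, power is low under either analysis, so the change improves the comparison without making it decisive. The pooled pre-post reading is much less affected from about 40% prevalence upward under the larger assumed effect. The primary weight outcome is not touched. The change is worth making because it costs little, but the evidence does not show that the planned result would be uninformative.

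**What to change.** For food insecurity, prespecify a comparison between the two randomised arms of the proportion of participants food insecure at baseline who are food secure at week 16. Label it exploratory and give a confidence interval. Report new food insecurity among those secure at baseline separately, state the baseline prevalence in each arm, and keep the all-participant change alongside.

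For depression, compare week-16 scores between the randomised arms in all participants, adjusted for the baseline score. Show any above-threshold subset only as supportive.

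Do not interpret pre-post change within a subset chosen for high baseline scores, because regression to the mean would produce apparent improvement without any effect. The comparison between arms avoids this: baseline surveys are collected before allocation, so the subset is defined before randomisation.

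The cost is analysis wording. Both surveys are already scheduled at baseline and week 16, and no entry criterion changes. The downside is a small food-insecurity subset with a wide interval, which is why it should not be presented as confirmatory.

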Study activity	Baseline visit (W0)	Week 2 (W0–W2)	Week 3 – 15 (W3–W15)	Week 16 visit (W16 ± 7 days)	6 months	12 months
Informed consent process	x					
Anthropometric data (weight, height, and blood pressure)	x			x	x	x
HbA1c	x			x	x	x
Completion of study questionnaires	x			x		
Individual nutrition counseling session		x				
Nutrition education videos			x			

**Table 2. tbl2:** Expected viewership of nutrition education videos

	Video title			
	Introduction to nutrition	Nutrition and weight loss	Nutrition and diabetes	Nutrition and hypertension
All participants	x	x		
Participants with pre-/type 2 diabetes			x	
Participants with hypertension				x
Participants with pre-/type 2 diabetes AND hypertension			x	

The control group will comprise 70 participants matched to intervention group participants based on BMI, diagnosis of pre-type 2 diabetes/type 2 diabetes, and/or hypertension. Control group participants will be identified from the electronic medical record, Epic^®^, after enrollment of all intervention arm participants has been completed. A flow chart of participant recruitment and completion of study activities is shown in Figure 1. Our study protocol adheres to the SPIRIT guidelines for clinical trial protocols (Chan *et al.*, 2013) and is registered on ClinicalTrials.gov with identifier NCT05174078.

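### The three-group ANOVA cannot be fitted as written for the survey outcomes, and the randomised comparison that remains does not answer the survey aim

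*Protocol article*

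**What the plan says.** All references are to the protocol article.

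- **Model.** Data analysis: "Separate repeated-measures ANOVAs will be conducted for each dependent variable with the between subjects factor group (healthy meals, produce box, and matched controls"), crossed with "the within subjects factor time (pre-intervention and 16 weeks"). No outcome is exempted.
- **Outcomes covered.** The same section lists as secondary dependent variable (iv) the "change in numeric rating from baseline to 16 weeks for food insecurity, diet quality, depression as well as self-efficacy for health eating, healthy weight"; the sixth score is self-efficacy in managing chronic disease.
- **Survey collection.** Survey data: the questionnaires "will be administered at baseline and at the 16-week follow-up visit". Table 1 places them at those two visits only.
- **Controls.** Study design: "Control group participants will be identified from the electronic medical record", once all intervention participants have been enrolled. The Abstract calls this retrospective chart review.
- **Survey aim.** Study aims, third aim: whether either food intervention, with counselling and education, "results in improvement in food insecurity, diet quality, depression, self-efficacy for healthy eating and healthy weight" and in chronic disease self-efficacy, from baseline to 16 weeks. It names no comparator, whereas the first two aims name the matched controls.
- **Effect sizes.** Data analysis: "Effect sizes will be calculated between pre-intervention and 16 weeks to capture the changes from pre- to post-intervention".

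**The concern.** The model rule and the data collection do not fit together. One of the three groups has no planned source of data for any of the six survey domains, so an analyst following the rule literally has no model to fit.

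The larger issue is what can be concluded. The third aim asks whether receiving either package improves the scores. The Abstract speaks of assessing the effect of the interventions on these domains, and Strengths and limitations counts that assessment as a strength. Without untreated survey data, a change over 16 weeks mixes any intervention effect with time trend and with altered reporting by participants who know that they received free food and counselling. Strengths and limitations acknowledges that there is no parallel control group but does not connect this to the survey outcomes. It also acknowledges that assessors of self-reported data are unblinded. Its remedy, collecting baseline self-report before allocation, protects the baseline score and not the 16-week score.

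**Working it through.** **The plan's own figure.** The article gives no figure for the survey outcomes. Its only computed design figure is 28 per group for weight, and it reproduces. With means 92, 78.4 and 85.2 kg (grand mean 85.2) and SD 16, the noncentrality is n × (6.8² + 6.8² + 0²)/16² = 0.36125n. On 2 and 3n − 3 degrees of freedom at alpha 0.05, power is 0.789 at n = 27 and 0.805 at n = 28. The point below does not depend on it.

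**Step 1: can the model be fitted?** It needs a score at two times in three groups.

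| Group | Baseline survey | 16-week survey |
|---|---|---|
| Meals (35) | yes, study visit | yes, study visit |
| Produce (35) | yes, study visit | yes, study visit |
| Matched controls (70) | no source given | no source given |

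Controls have no study visits and are chosen retrospectively, so there is no point at which a baseline survey could be given. The article nowhere plans to survey them or to take these scales from the chart. That they have no survey data is therefore an inference from the Abstract, Study design and Survey data sections; it is not stated outright.

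Satisfaction, if it counts as a dependent variable, fits the model even less well: "the post-intervention survey contains 11 non-validated items assessing adequacy, practicality, and satisfaction with healthy meals or produce box received by participants", so it has neither a control value nor a baseline value.

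**Step 2: what remains?** A two-group by two-time ANOVA. Its group-by-time interaction compares change between two arms randomised 1:1, and it is a valid test. At 80% power and two-sided 0.05 (noncentral t), it detects a standardised difference of about 0.68 with 35 per arm, 0.71 with 32 and 0.76 with 28. Both arms receive food, counselling and videos, so the contrast shows only how one package does relative to the other.

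**Step 3: what does the third aim rest on?** On change over time within the treated participants. As an illustration, take a one-sample t test of change at two-sided 0.05, pooled over both arms, with no intervention effect but a background drift d towards better scores, in SDs of the change score. The noncentrality is d√n. The chance of a significant result in the improving direction is:

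| Assumed drift d | n = 70 | n = 56 (2 × 28) |
|---|---|---|
| 0 | 2.5% | 2.5% |
| 0.1 | 13% | 11% |
| 0.2 | 38% | 31% |
| 0.3 | 70% | 60% |
| 0.4 | 91% | 84% |

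The drift values are assumptions; the article gives none.

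**Step 4: precision of the two-arm analysis.** Let each score have variance σ² at both times and correlation ρ between them. The per-participant variance is 2σ²(1 − ρ) for the change score and σ²(1 − ρ²) for ANCOVA on the 16-week score. The ratio is (1 − ρ²)/[2(1 − ρ)] = (1 + ρ)/2, which is 0.75 at ρ = 0.5 and 0.85 at ρ = 0.7. Both correlations are assumed.

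**The case against.** The strongest reply is that this is one over-general sentence in a condensed article. The third aim names no controls, the Abstract describes the survey analysis as pre-post change, and the surveys are tied to visits that only the food arms attend. An analyst would drop the empty level, and the stated model would then still deliver the randomised comparison. This stands in part. A reader might infer that only uncontrolled within-arm change is left and that meals versus produce is not planned at all; the article does not support that, because the interaction in the reduced model is that comparison.

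Four further points on that side are fair:

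- The aim is phrased as a question and concerns the food together with counselling and education, so the article has not already claimed that food alone improves the scores.
- Regression to the mean is a weak argument here, because entry is not selected on survey scores. Time trend and reporting bias carry the concern.
- A routine chart might hold a depression or food-insecurity screen for some controls. The article does not plan to use one.
- A group-by-time test in randomised arms is valid. ANCOVA improves precision; its absence is not an error.

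Two things survive. The rule covers each dependent variable without exception, which is wrong as written whatever a fuller plan may add. And the third aim asks a question that the remaining valid comparison cannot answer.

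**Conclusion.** The concern holds in a limited form. The three-group model cannot be fitted for the six survey domains, on the well-supported inference that the controls have no survey data. The randomised comparison of meals with produce survives and is valid, but it does not address whether either package improves the scores. That would rest on uncontrolled change, where even modest drift makes an apparent improvement likely: 13% to 91% for assumed drifts of 0.1 to 0.4 SD of the change score with 70 participants. The general disclosure of limitations does not cover this, since it is not linked to the survey outcomes.

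The consequence is confined to secondary outcomes. The primary outcome, weight at 16 weeks, and the sample size are unaffected.

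**What to change.** 1. Limit the three-level group factor to outcomes that are available in the chart for controls.
2. For the survey scores, specify a two-level factor, meals versus produce. Preferably analyse the 16-week score by ANCOVA adjusted for the baseline score, and report the between-arm difference with a 95% confidence interval.
3. Label within-arm pre-post changes and their effect sizes as descriptive.
4. Reword the third aim as describing change within each arm and estimating the difference between arms, with no causal claim of improvement.
5. In Strengths and limitations, say that the missing control group applies to the survey outcomes in particular.
6. Summarise satisfaction by arm at 16 weeks, outside the repeated-measures model.

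The cost is wording and a simpler model, with no new data or participants. The sponsor gives up only a conclusion about improvement that the design cannot support.

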### Sample size determination

Similar past research conducted in the US (Berkowitz, Delahanty, *et al.*, 2019) was used to estimate a baseline weight of 92 ± 16 kg for the study population. In order to estimate the effect size of weight loss potential in the intervention groups, the CDC healthy eating standard range of 1 to 2 pounds weight loss per week was used. The estimate for weight loss in the healthy meals group was 2 pounds per week over 15 weeks, and the estimate weight loss for the produce group was 1 pound per week for 15 weeks. It was assumed that there would be no weight change in the matched controls (standard of care) group. A one-way AONVA sample size calculation was performed using the following parameters: mean weight (kg) [matched controls 92, healthy meals 78.4, Produce 85.2], standard deviation 16 for all groups, 0.80 power, and 0.05 alpha. This yielded a sample size of 28 per group. We assume a 10% attrition rate, bringing the sample size to 35 per group.

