### Randomization

Randomization of participants will be conducted using the central randomization module available in the Research Electronic Data Capture (REDCap) program, a secure online database that will be utilized for data collection and management (Harris *et al.*, 2009, 2019). Randomization and allocation will occur in blocks of four. The allocation sequence was generated for a total of 80 participants using randomization software in the Sealed Envelope website (https://www.sealedenvelope.com/simple-randomiser/v1/lists) and uploaded into our study’s REDCap database. Following consent into the study and collection of all baseline data, study participants will be randomly allocated to the healthy meals or produce box group in a 1:1 ratio using the randomization sequence pre-entered into REDCap.

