## Data collection

### Demographic and clinical data

Participants’ date of birth, sex, race, and ethnicity will be collected as part of demographic data. Objective health data that will be collected are weight, height, hbA1c, blood pressure, prediabetes/diabetes diagnosis and classification, hypertension diagnosis and classification, diabetes and blood pressure medications, and comorbid chronic conditions. These data will be collected in-person at the baseline visit and at 16 weeks from baseline and via chart review of routine care at six and 12 months from enrollment in the study.

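### For meals versus produce, the planned two-time-point ANOVA is an unadjusted test of change; adjusting for baseline would cost nothing, with a small gain for weight and possibly a larger one for secondary outcomes

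*Protocol article*

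**What the plan says.** The Data analysis section of the protocol article sets one method for all outcomes: "Separate repeated-measures ANOVAs will be conducted for each dependent variable with the between subjects factor group" (meals, produce, matched controls). The second factor is "the within subjects factor time (pre-intervention and 16 weeks"). No baseline covariate is named. On the primary outcome the section says: "The primary dependent variable (outcome) is absolute weight change at 16 weeks between groups".

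The baseline data exist. For the clinical measures, which include weight, HbA1c and blood pressure, the Demographic and clinical data section says: "These data will be collected in-person at the baseline visit and at 16 weeks from baseline". The Survey data section says that the questionnaires "will be administered at baseline and at the 16-week follow-up visit". The Randomization section puts all of this ahead of allocation: "Following consent into the study and collection of all baseline data, study participants will be randomly allocated". One outcome has no baseline, because "the post-intervention survey contains 11 non-validated items assessing adequacy, practicality, and satisfaction".

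Only the meals and produce arms are randomised. The 70 controls are matched patients found in the medical record after enrolment, and the Study design section itself calls them nonequivalent.

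**The concern.** A repeated-measures ANOVA may look as though it uses the baseline value as a covariate would. With two time points it does not. Its group-by-time term compares mean change between groups, which fixes the coefficient on baseline at 1 instead of estimating it. (The group main effect averages the pre and post values and would be a poorer test still.)

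For two randomised arms this has two consequences. When the correlation between baseline and follow-up is below 1, the change score carries noise that a baseline-adjusted model would remove. And a chance difference in starting values passes partly into the estimated difference in change. The protocol names its small sample as a limitation and says that attrition threatens power, so precision available from data already in hand is worth taking.

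**Working it through.** **The plan's own figure.** The Sample size determination section uses a one-way ANOVA on final weights: means 92, 78.4 and 85.2 kg, SD 16, alpha 0.05, power 0.80. The noncentral F gives power 0.789 at 27 per group and 0.805 at 28, so the stated 28 per group reproduces. That calculation uses no baseline-to-follow-up correlation.

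**Equivalence.** On simulated data with three groups and two times, the group-by-time F and the one-way F on change were both 4.03996.

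**Precision.** Let s be the SD, taken as equal at both times, and rho the baseline-to-16-week correlation.

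- Change score: residual variance 2s²(1 − rho)
- Baseline-adjusted: residual variance s²(1 − rho²)
- Ratio, adjusted to change: (1 + rho)/2

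The protocol gives no rho for any outcome, so every row below is an assumption. The simulated ratios come from 6,000 runs with 35 per arm.

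| Assumed rho | (1+rho)/2 | Variance gain | Simulated ratio |
|---|---|---|---|
| 0.40 | 0.70 | 30% | not run |
| 0.50 | 0.75 | 25% | 0.78 |
| 0.70 | 0.85 | 15% | 0.87 |
| 0.90 | 0.95 | 5% | 0.96 |
| 0.95 | 0.975 | 2.5% | 0.997 |

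The simulated ratios lie slightly above the formula, which is asymptotic and ignores the small cost of estimating the slope. At rho 0.95 almost nothing is gained at this sample size.

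**Power, meals versus produce.**

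- Weight: planned difference 85.2 − 78.4 = 6.8 kg, 28 per arm, rho 0.9. Power is 0.945 with change scores and 0.954 with adjustment.
- A generic secondary outcome: 31 per arm (35 × 0.9 = 31.5) and an assumed difference of 0.6 baseline SD. Power goes from 0.56 to 0.72 at rho 0.4, from 0.64 to 0.77 at rho 0.5, and from 0.85 to 0.90 at rho 0.7.
- In participants, the change-score test needs 1/0.70 = 1.43 times as many at rho 0.4 and 1/0.85 = 1.18 times as many at rho 0.7.

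**Chance imbalance in weight.** The protocol's planning value for baseline is that past research "was used to estimate a baseline weight of 92 ± 16 kg for the study population".

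- Standard error of the baseline difference between two arms of 35: 16 × √(2/35) = 3.82 kg.
- Planned losses: (92 − 78.4)/92 = 14.8% for meals and (92 − 85.2)/92 = 7.4% for produce; the average is 11.1%.
- If loss is proportional to starting weight in each arm, a one-standard-error imbalance split evenly between the arms shifts the contrast by 0.111 × 3.82 = 0.42 kg, about 6% of the planned 6.8 kg.
- Expressed through rho instead, the shift is (1 − rho) × 3.82: 0.38 kg at rho 0.90 and 0.19 kg at 0.95. This is another description of the same effect and is not additional to it.

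In the simulation the change-score estimate correlated with the baseline imbalance at −0.49, −0.39 and −0.24 for rho 0.5, 0.7 and 0.9. The adjusted estimate correlated at about zero.

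**The case against.** The strongest reply is that the stated method is valid. Under randomisation the change-score contrast is unbiased on average, and it tests the outcome as the protocol defines it. This stands: the point is about efficiency and about imbalance in the one sample that is realised. It does not defend the choice, because modelling change with baseline as covariate gives the same group effect as modelling the 16-week value, so the stated outcome need not alter.

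A second reply is that an article may leave covariates to a fuller plan. But the article does name a method for each outcome. If a fuller plan already adjusts for baseline, this sentence should be brought into line with it.

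Third, the gain is smallest on the primary outcome, and the larger gains fall on outcomes that the protocol partly labels exploratory. The survey aim is mainly about improvement from baseline to 16 weeks, which the time term addresses. Both remarks are right, and they limit the size of the point.

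Fourth, the primary aim also compares both arms with matched controls. A reader might infer that baseline adjustment would sharpen or de-bias those contrasts as well. The documents do not support that. The controls are not randomised, adjustment does not remove confounding, and with nonequivalent groups the change-score and adjusted estimates can target different quantities.

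A reader might also put the carry-over at 0.148 × 3.82 = 0.57 kg. That applies the meals arm's planned loss to both arms; the protocol's own losses for the two arms give 0.42 kg.

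**Conclusion.** The point holds for the randomised meals-versus-produce contrast, on outcomes that have a baseline value. There the planned test is an unadjusted test of change, and a model at least as precise asymptotically is available from data already collected.

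Its size rests on assumed correlations. At rho 0.90-0.95 the variance gain for weight is 2.5-5%, so the primary test is barely affected. At rho 0.4-0.7 the gain for HbA1c and survey scores would be 15-30%; that their correlations are lower than for weight is itself an assumption. The carry-over of about 0.4 kg assumes proportional loss at the planned rates and a one-standard-error imbalance.

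It would go too far to say that the planned analysis is invalid, that precision is lost on every outcome and contrast, or that every outcome has a baseline; the satisfaction items do not. The change is worth making because it is nearly free, although the trial does not fail without it.

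**What to change.** In the Data analysis section:

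- For meals versus produce, on every outcome with a baseline value, make the main analysis a model of the 16-week value (or of change) on group plus that outcome's own baseline. A baseline-constrained mixed model is an alternative, and it can also keep participants with one missing value.
- Exclude the satisfaction items, which are measured only after the intervention.
- Keep the time term for the pre-to-post survey aim.
- For contrasts with the matched controls, keep the change-score estimate and show the baseline-adjusted estimate as a sensitivity analysis.

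The cost is a few lines of text and one model term, with no new data and no added burden on participants. The small downside is that the two estimates may differ for the control contrasts, so the text should say in advance which one leads.
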